### Data analysis

Agreement between the triage decisions from live-online assessments will be calculated using percentage agreement and kappa statistics, reported with 95% confidence intervals. This will also be calculated for the triage decisions from live-live assessments. Comparison of the difference in levels of agreement between the live-online group and the live-live group will be the primary measure of the reliability of the online assessment and is the basis for the sample size calculation for this project. Online assessment will be taken to be non-inferior to live assessment if percentage agreement in the live-online group is not more than 15% less than the percentage agreement in the live-live group.

The online assessment can be regarded in a similar manner to a diagnostic test, where the interest is in the number of patients recommended for a higher level of care from the online assessment compared with live assessment (i.e. false positives, specificity), and in the number of patients where important clinical diagnoses are missed in an online assessment (i.e. false negatives, sensitivity).

These measures will therefore be calculated and reported. Exploratory analyses of patient characteristics will be undertaken to examine these cases where differences of triage decision are identified. Agreement between the online and live detection of common geriatric syndromes will also be assessed using kappa statistics.

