## Methods/Design

### Setting and participants

The study will be conducted at 3 large Australian hospitals: Princess Alexandra Hospital, Brisbane, Queensland; Box Hill Hospital, Box Hill, Victoria; and The Northern Hospital, Melbourne, Victoria. As the study is designed to evaluate the performance of the online approach when delivered by professionals with experience in using the interRAI AC instrument, at Box Hill Hospital and The Northern Hospital, where the nurses and geriatricians are new to the approach, there will be a "run in" series of 25 cases per geriatrician. This study has been approved by the Human Research Ethics Committee at each site and UQ.

All acutely hospitalised patients referred to the geriatric consultation service at each site will be considered for inclusion in the study. Patients who have previously been consented and reviewed for the study (in a former hospital episode) and those who are already known to one of the study geriatricians will be excluded.

Consent for participation in the study will be secured by the nurse administering the interRAI AC instument prior to the commencement of the consultation. Non-consenting patients will receive the "normal" geriatric consultation for the hospital site. Full demographic and limited clinical information will be secured for non-consenting subjects to enable examination of potential bias. We anticipate consent rates in excess of 95% based on previous research experience with similar subjects, and on the experience of a previous pilot study [8].

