### Study design

The design aims to measure the level of agreement in triage decisions made "online" with those made for the same patient at "live" assessment, and to compare this with the level of agreement between two independent geriatricians each assessing a patient at a live consultation. The aim is to distinguish decision disagreement attributable to the online format of assessment from the 'usual' inter-geriatrician differences in clinical decision making. It is beyond the scope of this study to establish the "online-online" inter-rater reliability; this will be examined in a subsequent study and reported separately.

Each consenting patient will undergo sequential assessment by two independent geriatricians, designated "geriatrician 1" (G1) and "geriatrician 2" (G2), in one of the following randomly allocated configurations: live-live (G1-G2), live-live (G2-G1), online-live (G1-G2) or online-live (G2-G1). The patient recruitment and randomisation process is outlined in Figure 1.

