### Randomisation

The following process for randomisation will be carried out by the statistician. The < ralloc > command will be used to generate 2 separate randomisations in Stata version 10.1. These allocations will then combined to create the individual patient allocation to geriatrician/intervention and stored in individually numbered opaque envelopes for each site. Initially, patients will be equally randomised to the 4 intervention arms in blocks of 4 and 8. Patients will then be equally randomised to the 2 intervention arms (geriatricians 1 and 2) in blocks of 2 and 4. Due to the constraint that a maximum of two patients are to be randomised on any one day and the same geriatrician must not be used for both, the second of the two patients is deterministically allocated to the doctor who does not attend to the first of the two patients. Allocations will be approximately balanced across 3 studies centres.

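### Allocation is organised by site, but agreement and kappa are described only by group; stratifying by site is a free, modest improvement

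*Protocol article*

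**What the plan says.** **Allocation (Randomisation).** Within the first allocation, "patients will be equally randomised to the 4 intervention arms in blocks of 4 and 8", so online-live and live-live are 1:1. Allocations are "stored in individually numbered opaque envelopes for each site", and "Allocations will be approximately balanced across 3 studies centres". When two patients are randomised on one day, the second goes to the doctor who did not see the first. That reads as two doctors at each site.

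**Sites and raters (Setting and participants; Study design).** "The study will be conducted at 3 large Australian hospitals". Two of them have a run-in series because they are places "where the nurses and geriatricians are new to the approach", which suggests that geriatricians belong to a site. "Each consenting patient will undergo sequential assessment by two independent geriatricians", labelled G1 and G2. The article does not say outright that each site has one pair of its own.

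**Analysis (Data analysis).** "Agreement between the triage decisions from live-online assessments will be calculated using percentage agreement and kappa statistics, reported with 95% confidence intervals". The live-live group is treated in the same way, and the comparison of the two groups is the primary measure. Online assessment is non-inferior "if percentage agreement in the live-online group is not more than 15% less than the percentage agreement in the live-live group". Kappa is reported beside percentage agreement for triage and is the only measure named for the geriatric syndromes. The section mentions neither site nor rater pair.

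**The concern.** The Study design section sets out to separate disagreement caused by the online format from the ordinary differences between geriatricians. That contrast is most naturally made within a pair, and allocation by site supports it. An analysis by group alone leaves two things open.

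- **Percentage agreement.** If pairs differ in how often they agree, the crude standard error includes between-site variation that site-balanced allocation has already removed from the comparison. The interval is then a little wider than the design requires.
- **Kappa.** Chance agreement depends on how often residential care is recommended. If that rate differs by site, collapsing the sites lets between-site differences count as agreement beyond chance.

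Also, the only planned look at disagreement is by patient characteristics, so the article describes no display that would show whether one site's pair drives the result.

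**Working it through.** **Inputs from the article:** 114 per arm, assumed agreement 60%, margin 15 points, two-sided 5% (one-sided 2.5% for non-inferiority), three sites, 1:1 allocation. **Assumed:** three equal sites, and all site-specific agreement and recommendation rates. The agreement and kappa illustrations are separate sets of assumptions.

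**1. The plan's own figure.** The attrition step reproduces: 228/0.85 = 268.2. The 114 per arm does not: 2 × 0.24 × (1.960 + 0.842)² / 0.15² gives 168 per arm at one-sided 2.5%, and 132 at one-sided 5%. With 114 per arm the crude standard error is √(2 × 0.24/114) = 0.0649, and power is Φ(0.15/0.0649 − 1.960) = 63.7%. That shortfall is a separate matter; 63.7% serves here only as the baseline.

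**2. Difference in percentage agreement.** With balanced allocation the crude and stratified estimates coincide. The crude formula uses p(1−p) = 0.24; the stratified one uses the mean of p_s(1−p_s) over sites.

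| Site agreement | Mean p_s(1−p_s) | Variance saved | SE | Power |
|---|---|---|---|---|
| 60/60/60% | 0.2400 | 0 | 0.0649 | 63.7% |
| 55/60/65% | 0.2383 | 0.7% | 0.0647 | 64.0% |
| 50/60/70% | 0.2333 | 2.8% | 0.0640 | 65.0% |
| 45/60/75% | 0.2250 | 6.25% | 0.0628 | 66.5% |
| 40/60/80% | 0.2133 | 11.1% | 0.0612 | 68.9% |

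At 40/60/80%, 80% power would still need 149 per arm, so stratifying does not close the gap.

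**3. Kappa.** Let both raters at site s recommend residential care at rate p_s, with a common within-site kappa k. Disagreement at the site is (1−k) × 2p_s(1−p_s). With P the mean rate, this gives

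1 − pooled kappa = (1−k) × mean[p_s(1−p_s)] / [P(1−P)].

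For k = 0.30:
- 30/30/30%: the ratio is 1, so pooled kappa is 0.30.
- 20/30/40%: 0.2033/0.2100 = 0.968; pooled kappa = 1 − 0.70 × 0.968 = 0.32.
- 15/30/50%: 0.1958/0.2164 = 0.905; pooled kappa = 0.37.
- 10/30/60%: 0.1800/0.2222 = 0.810; pooled kappa = 0.43.

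**4. Pooling can also lower kappa.** Let the two raters' rates be 20 v 40%, 40 v 20% and 30 v 30% at the three sites, with k = 0.30 throughout. Expected disagreement by chance is 0.44, 0.44 and 0.42, with mean 0.4333; for the pooled table it is 0.42. Pooled kappa = 1 − 0.70 × 0.4333/0.42 = 0.28.

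**5. Effect on the contrast between arms.** Both arms share the site mix, so both kappas move in the same direction. Within-site kappas of 0.40 and 0.20 differ by 0.20. After pooling they differ by 0.19 at 20/30/40%, 0.17 at 10/30/50% and 0.15 at 10/40/70% (0.55 against 0.40). The gap narrows, but only slightly unless rates are far apart.

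**The case against.** The strongest objection is that this is read from silence. The Data analysis section names measures and groups; it never says that sites will be pooled or ignored, and it gives no interval method. A stratum term or a stratified kappa is detail that a condensed article may leave to an SAP, and nothing in the article contradicts a stratified analysis. This stands: the point is a request to state or confirm the analysis, not an error in the text. One pair per site is likewise an inference, though the same-day rule in the Randomisation section makes it a reasonable one.

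Three stronger readings are tempting and are not supported.

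- A reader might infer that the stated intervals are invalid or could falsely declare non-inferiority. Ignoring a balanced site factor errs the other way, and by little under modest spreads.
- A reader might infer that pooled kappas are necessarily inflated. They are unchanged if recommendation rates are equal and can fall if rater tendencies oppose each other (0.30 to 0.28). No site rates are given, and 0.43 needs a spread from 10% to 60%.
- A reader might infer that the primary conclusion is at risk from kappa. The 15-point rule is set on percentage agreement.

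It is also fair to say that stratifying by site conditions on the pairs taking part. It does not address whether a few pairs stand for geriatricians in general; a table by site makes that limit visible but does not remove it.

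What survives is that the described analysis does not use the grouping by which allocation is organised, and that using it costs nothing.

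**Conclusion.** The point holds as a low-cost recommendation. The crude comparison of percentage agreement is valid and slightly conservative: it loses about 0 to 3% of variance if site agreement lies within 10 points of 60%, and 6% at 45/60/75%, where power at 114 per arm would rise from 63.7% to 66.5%. Pooled kappas can overstate within-pair agreement, by about 0.02 for a modest spread in recommendation rates and 0.13 for a wide one, and can occasionally understate it. This bears on the reported kappas for triage and syndromes, not on the primary rule. The sizes rest on assumed site rates and equal sites, and the rater-pair argument rests on the inference that geriatricians are site-specific.

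**What to change.** State in the analysis section or the SAP, or confirm if the SAP already says so, that:

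1. the difference in percentage agreement (online-live minus live-live) is estimated stratified by site, for example by Mantel-Haenszel or stratified Miettinen-Nurminen, with non-inferiority judged by whether its lower 95% limit lies above −15 points;
2. kappas for triage and for the geriatric syndromes are computed within site and combined as stratified kappas;
3. agreement by arm is tabulated for each site, and for each pair if a site uses more than one.

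The cost is a sentence or two and one table, with no further patients or data. The sample-size shortfall needs its own correction.

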**Discussion:**

If the online approach is found to be less precise than live assessment, further analysis will seek to identify patient subgroups where disagreement is more likely. This may enable a protocol to be developed that avoids unsafe clinical decisions at a distance.

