An innovative web based model of comprehensive geriatric assessment has been developed by The Centre for Research in Geriatric Medicine (CRGM) at the University of Queensland (UQ)[3,4]. This system utilises the interRAI Acute Care (AC) instrument, a validated assessment tool developed by the interRAI international collaborative to support evaluation of older people in acute hospital settings [5]. The interRAI AC comprises 121 individual clinical items that profile the pre-morbid and current status of the patient. The individual items have been shown to be clinically relevant and to have overall "substantial" levels of inter-rater reliability [6]. The interRAI AC incorporates screeners for common geriatric syndromes, risk assessment tools for adverse outcomes and a range of scalar measures that enable assessment of severity or dependency in the domains of pain, cognition, communication, and activities of daily living. It also includes algorithms to identify patients most likely to benefit from preventive or curative interventions, along with guidelines for further management. The instrument is administered by trained nurses who collect standardised patient data, and enter it onto a web based database. This data is then used by the geriatrician to facilitate patient assessment and provide recommendations either "online" or in conjunction with an in-person consultation. The system has also been used to support case preparation for distance assessment using video-conferencing [7].

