**Figure 1 F1:**
[figure not shown]
**Procedure for patient recruitment and allocation to paired consultation method**.

The paired geriatricians will be blinded to the results of their colleague's assessment. In the case of live-live assessments the order in which the geriatricians consult the patient will be randomly allocated in order to minimise any systematic influence that the interaction of the first geriatrician with the patient may have on the second assessment.

In all cases, the interRAI AC instrument will be administered by a trained nurse. Once these findings have been entered by the nurse into the software system, a geriatrician consultation will follow. Paired geriatrician assessments will be completed in the time it usually takes for a geriatrician assessment to occur following referral to the geriatrician consultation service at that site.

For live assessments, the assessing geriatrician will have access to the interRAI AC instrument data online. The geriatrician will also be able to read the medical record. The nurse will not interact directly with the geriatrician, in order to reduce the risk of contamination of decisions when consecutive live assessments are made.

For online assessments, the geriatrician will have access to the interRAI AC instrument data online only. The geriatrician will conduct the assessment without direct contact with the nurse. The geriatrician will not have access to the medical record. However, any online test results (e.g. radiology and pathology) which are usually accessed electronically will be available to both doctors, replicating the process that would occur in a distance assessment.

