### Sample size and power analysis

The outcome of interest will be the difference in percentage agreement between paired assessments for live-live arm and online-live arm for the question: "is residential care recommended?", scored as "yes" (1) or "no" (2). A non-inferiority study tests whether the percentage agreement between clinicians in an intervention arm (online-live) does not lie beyond the lower limit of an acceptable range (a one-tailed area of clinical indifference) when compared with the standard clinical practice arm (live- live).

The sample size of 288 subjects (114 online-live, 114 live-live) was identified to provide the study with power exceeding 80% to detect a non-inferiority margin of 15% for levels of agreement between online-live when compared with live-live arms for the decision "yes, residential care is recommended". This is based on an assumption of inter-geriatrician agreement of 60% for geriatric triage decisions [8], allowing a two-sided type 1 error rate of 5%. With a 15% allowance for attrition, the adjusted sample size is 268 (i.e. 228/(1-0.15)). After rounding, 270 cases will be required in total between all sites.

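### The primary difference in percentage agreement could be adjusted for interRAI AC scales already recorded for every patient: an optional and modest gain in precision, not an error

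*Protocol article*

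**What the plan says.** The Data analysis section states that "Comparison of the difference in levels of agreement between the live-online group and the live-live group will be the primary measure" of the reliability of online assessment. Online assessment is accepted if "percentage agreement in the live-online group is not more than 15% less than the percentage agreement in the live-live group". Agreement within each arm is to be "calculated using percentage agreement and kappa statistics, reported with 95% confidence intervals". The Sample size section sizes the trial on "the difference in percentage agreement between paired assessments for live-live arm and online-live arm" for a yes/no question on residential care. No adjusted estimator is named, and none is excluded.

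On patient characteristics, the Background describes the interRAI AC as including "a range of scalar measures that enable assessment of severity or dependency in the domains of pain, cognition, communication, and activities of daily living". In the Study design section (text after Figure 1), "In all cases, the interRAI AC instrument will be administered by a trained nurse", and the geriatrician consultation follows once the findings are in the software. The Discussion paragraph of the Abstract says that, should online assessment prove less precise, "further analysis will seek to identify patient subgroups where disagreement is more likely". Data analysis plans exploratory work on patient characteristics in cases where triage decisions differ. The Randomisation section names no patient characteristic as a stratifier.

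**The concern.** The authors think it plausible that some patients are harder to agree on than others, and they hold standardised measures of cognition, communication and daily function for everyone. If those measures predict whether a pair of geriatricians agrees, the unadjusted difference carries variance that could be removed at almost no cost. Precision is scarce here: on the article's own inputs the 95% interval is nearly as wide on each side as the margin, so even a small reduction raises the chance of a conclusive answer.

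**Working it through.** **Inputs.** From Sample size and power analysis: 60% agreement (taken as equal in both arms), 114 pairs per arm, a 15-point margin, two-sided 5% (one-sided 2.5%), and power above 80%. The printed total of 288 does not match 114 + 114 = 228; the per-arm figure is used here. The share of variance in the agreement indicator explained by baseline scales (R²) is not in the article. It is an assumption, shown over a range.

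**1. The plan's own figure.** n per arm = (1.960 + 0.842)² × 2 × 0.6 × 0.4 / 0.15² = 7.849 × 0.48 / 0.0225 = 167.4, so 168, not 114. (At one-sided 5% it is 132.) With 114 per arm:
- SE = √(0.48/114) = 0.0649
- 95% half-width = 1.96 × 0.0649 = 12.7 points
- power = Φ(0.15/0.0649 − 1.96) = Φ(0.352) = 63.7% (74.8% at one-sided 5%)

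**2. Effect of adjustment.** Multiply the variance by (1 − R²), assuming the scales act equally in both arms:

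| R² | Half-width (points) | Power, 114 per arm | n per arm for 80% |
|---|---|---|---|
| 0 | 12.7 | 63.7% | 168 |
| 0.02 | 12.6 | 64.6% | 165 |
| 0.05 | 12.4 | 66.0% | 160 |
| 0.10 | 12.1 | 68.3% | 152 |
| 0.20 | 11.4 | 73.4% | 135 |
| 0.30 | 10.6 | 78.9% | 118 |

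**3. Which R² is plausible for a yes/no decision.** Suppose each of two interchangeable, independent geriatricians recommends residential care for a given patient with probability p. They agree with probability p² + (1 − p)² = 1 − 2p(1 − p), which is never below 50%. Overall agreement of 60% requires E[p(1 − p)] = 0.2. Then R² = 4 Var[p(1 − p)] / 0.24, if the scales captured p completely. Two assumed distributions of p meet the 60% condition:
- Beta(2, 2), mean p 0.5: E[p²(1 − p)²] = 36/840 = 0.04286; variance 0.04286 − 0.04 = 0.00286; R² = 0.01143/0.24 = 0.048.
- Beta(6, 14), mean p 0.3: E[p²(1 − p)²] = 8820/212520 = 0.04150; variance 0.00150; R² = 0.00601/0.24 = 0.025.

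Real scales capture only part of p, so an R² of about 0.02 to 0.04 is a fair expectation, with power of about 65 to 66%. The ceiling under the 50% floor is (1 − 0.6)(0.6 − 0.5)/0.24 = 0.167 (power 71.6%). It is reached only if every patient sits at either 50% or 100% agreement.

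**4. Shape.** In this model agreement is lowest in the middle of the range. With p symmetric about 0.5, as in Beta(2, 2), a linear term in p explains none of the variation. Simulations with agreement lowest in the middle half of a severity scale showed the same: power with and without a linear term differed by 0.2 points.

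**5. Effect in the online arm only.** In 20,000 simulated trials with 60% agreement overall in each arm, and agreement of 45%/75% in two severity halves of the online arm alone, power went from 63.8% to 64.8%. With 40%/80% it went from 63.1% to 64.9%.

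**6. Can adjustment restore 80%?** The R² needed is 1 − 114 × 0.0225 / (0.48 × 7.849) = 0.32. With 135 per arm (270 and no attrition) it is 0.19. Both exceed the 0.167 ceiling in step 3.

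**The case against.** The strongest reply is that nothing here is wrong. An unadjusted difference between randomised arms is valid and matches both the decision rule and the sizing basis. Chance imbalance in case difficulty is already covered by its interval and its type I error. That stands in full.

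It is also fair that the article is a condensed account, that it does not rule out adjustment, and that covariates are commonly chosen in an analysis plan, which is not shown. The unadjusted reading is the natural one from the wording of the rule, but it is an inference.

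A reader might further infer that the plan expects patient characteristics to predict disagreement and then discards that knowledge. The text does not go so far. The subgroup search in the Abstract depends on online assessment proving less precise, and the work in Data analysis is labelled exploratory. No strength of association is given anywhere. That subgroup search also fits characteristics that matter only in the online arm, where the gain is smaller.

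Finally, entry before consultation is not the same as entry before allocation. The recruitment flow is in Figure 1, which was not available, so the order cannot be checked.

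What remains is that the scales are collected for everyone anyway and could be used without altering the margin or the scale of the result.

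**Conclusion.** This is an optional efficiency improvement. On the stated inputs the likely gain is 1 to 2 points of power over 63.7%, rising to about 5 points if R² reaches 0.10. These sizes rest on an assumed R², on equal agreement of 60% in both arms, and on scales that act in both arms and are modelled in a suitable form. A linear term could gain almost nothing.

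Two stronger conclusions might be drawn and are not supported. One is that the planned comparison is biased or invalid; it is neither. The other is that adjustment would rescue the power claim. It would not: 114 pairs per arm fall short of 80% from the article's own inputs, and that needs its own correction.

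**What to change.** In Data analysis, make the primary estimate a standardised (marginal) difference in percentage agreement. Fit a model for whether the pair agrees, on arm plus two or three pre-named interRAI AC scales, for example cognition and pre-morbid activities of daily living. Enter them in a non-linear form (quadratic or categorised), and average the predictions over all patients under each arm. Use only items recorded before allocation or unaffected by it. Give a robust 95% interval, judge it against the same 15-point margin, and report the unadjusted difference alongside. In simulations of an adjusted analysis of this kind, the rejection rate at a true 15-point loss was 2.3 to 2.9%, against a nominal 2.5%.

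The cost is wording only, with no new data. The scales and their functional form must be fixed in advance, and the analysis becomes slightly less simple to explain than raw percentages.

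### The stated non-inferiority rule is not tied to a confidence limit, so as worded it does not deliver the 5% type 1 error on which the sample size rests

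*Protocol article*

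**What the plan says.** In the Data analysis section, agreement in each arm is to be given as "percentage agreement and kappa statistics, reported with 95% confidence intervals". The section then names the primary analysis: "Comparison of the difference in levels of agreement between the live-online group and the live-live group will be the primary measure". It adds that the sample size was built on this comparison. The decision rule follows: "Online assessment will be taken to be non-inferior to live assessment if percentage agreement in the live-online group is not more than 15% less", with live-live agreement as the reference. The section specifies no interval or test for the difference, and it does not link the per-arm intervals to the decision.

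The Sample size and power analysis section uses the language of formal testing: "A non-inferiority study tests whether the percentage agreement between clinicians in an intervention arm (online-live) does not lie beyond the lower limit"; the range in question is described as one-tailed. It claims "power exceeding 80% to detect a non-inferiority margin of 15" per cent, on an "assumption of inter-geriatrician agreement of 60% for geriatric triage decisions", and "allowing a two-sided type 1 error rate of 5" per cent. It does not say that a confidence limit must clear the margin.

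**The concern.** A non-inferiority claim controls its false-positive rate only if sampling error enters the decision, usually by requiring a confidence limit for the difference to lie on the right side of the margin. A rule that asks only whether the two percentages differ by no more than the margin behaves like a coin toss when the true deficit equals the margin, whatever the sample size. Type 1 error and power as stated in the sample size section have no role in such a rule.

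The rule decides the trial's main conclusion. If the two sections stay unreconciled, an analyst could follow either one after seeing the data, and they can give opposite answers. Suppose 60% live-live and 45% live-online agreement are observed with 114 per arm. The deficit equals the margin, so the rule as worded is met. The standard error is √(0.60×0.40/114 + 0.45×0.55/114) = 0.0654, so the 95% interval is -15 ± 1.96×6.54, or about -28 to -2 points. That interval excludes zero and reaches nearly twice the margin.

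**Working it through.** **Inputs from the article**

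- Margin 15%, read as percentage points (Data analysis; Sample size and power analysis).
- Live-live agreement 60%, two-sided type 1 error 5%, power above 80%, 114 per arm (Sample size and power analysis).
- Total to recruit 270, which is 135 per arm if nobody is lost.

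**Assumptions added here**

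- Patients are independent; clustering by geriatrician pair or site is ignored.
- Power is calculated with true online-live agreement also at 60%.
- Two-sided 5% corresponds to one-sided 2.5% for non-inferiority.

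**Step 1. The plan's own figure.** The usual formula for two proportions, with equal true agreement p and margin m, is

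n per arm = 2p(1-p)(z₁₋α + z₁₋β)² / m²

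- One-sided 2.5%: 0.48 × (1.960 + 0.842)² / 0.0225 = 167.4, so 168 per arm.
- One-sided 5%: 0.48 × (1.645 + 0.842)² / 0.0225 = 131.9, so 132 per arm.

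Neither gives 114. Variants with the variance under the null, with a continuity correction, or with superiority formulas gave 120 to 186. The attrition step does reproduce: 228/0.85 = 268.2. The article prints "The sample size of 288 subjects (114 online-live, 114 live-live"), but 114 + 114 = 228, so the printed total appears to be a slip. The calculations below use 114 per arm.

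**Step 2. Chance of declaring non-inferiority.** Let X and Y be independent binomial counts of agreeing pairs in the live-live and live-online arms, n each. Exact probabilities are summed over all (X, Y) for two rules:

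- As worded: Y/n - X/n ≥ -0.15.
- Confidence interval rule: (Y/n - X/n) - 1.96 × SE > -0.15, with SE the Wald standard error of the difference.

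With n = 114 and live-live agreement 60%:

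| True live-online agreement | True deficit | As worded | 95% CI rule |
|---|---|---|---|
| 60% | 0 points | 99.1% | 63.6% |
| 45% | 15 points | 52.0% | 2.6% |
| 40% | 20 points | 23.6% | 0.3% |
| 35% | 25 points | 6.7% | 0.02% |

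**Step 3. Sensitivity of the error at the margin, rule as worded**

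- 135 per arm: 51.1% (95% CI rule 2.7%).
- 144 per arm, if the printed 288 were right: 49.4%.
- 114 per arm with live-live agreement of 70%, 80% or 90%: 52.1%, 52.3% and 52.9%.

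The result of about one half therefore does not depend on the 60% assumption or on the sample size.

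**Step 4. Power under a confidence interval rule, equal 60% agreement**

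- Normal approximation, n = 114: SE = √(0.48/114) = 0.0649; 0.15/0.0649 = 2.31; Φ(2.31 - 1.96) = 64%. Exact enumeration also gives 64%.
- n = 135: 71%.
- With a one-sided 95% limit instead: 74% at 114 and 81% at 135, with error at the margin of 4.6% and 4.6%.

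**The case against.** The strongest reply is that the sentence in the Data analysis section states the margin, not the test. It does not say that observed percentages alone decide. The same paragraph calls for 95% intervals and points to the sample size calculation, where a test, a 5% type 1 error and a power are all named. Read together, one section supplies the margin and the other the error rate. The choice of interval method can then be left to an analysis plan.

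Much of this stands. A formal test was probably intended, and a reader who infers that the trial would in fact run at a 50% error rate goes further than the article allows. The choice among interval methods is indeed not a matter for an article. But the article does not leave the criterion open: it states when non-inferiority will be concluded, and that statement contains no confidence limit. The intervals it mentions are for agreement within each arm, not for the difference. The sample size section never says that a limit must clear the margin. This is a rule stated loosely and at odds with the stated error rate, not a detail left out.

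Two stronger readings should be set aside.

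- A reader might take the 15% as relative, which at 60% agreement would be 0.15 × 60 = 9 points, with power of about 28% under a confidence interval rule. The sample size section defines the outcome as a difference in percentage agreement, so percentage points is the natural reading. The missing unit is only a minor point of wording.
- A reader might infer that the rule would certify an unreliable method as safe. The Data analysis section also plans kappa, recommendations for a higher level of care, missed important diagnoses and a look at discordant cases. These inform the safety conclusion too.

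**Conclusion.** The point holds for the rule as worded. At a true 15-point deficit it would declare non-inferiority about half the time (49% to 53% over the sizes and agreement levels tried), against about 2.6% under a two-sided 95% confidence interval rule. At 20 points the figures are 24% and 0.3%, with 114 per arm and 60% live-live agreement. The consequence is a false non-inferiority declaration on the primary measure.

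The figures rest on independent patients and an absolute margin. The result at the margin is insensitive to the agreement level. The power figures are not: with 114 per arm, power under the two-sided 95% rule rises to 70% at 70% agreement and 81% at 80% agreement. The article, however, assumes 60%.

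**What to change.** Replace the decision sentence in the Data analysis section with: *Online assessment will be declared non-inferior only if the lower limit of the two-sided 95% confidence interval for the difference in percentage agreement (live-online minus live-live) lies above -15 percentage points.* This links the decision to the error rate in the sample size section and settles the unit of the margin. The interval method, for example Newcombe or Farrington-Manning, can be named in the analysis plan.

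The edit is one sentence, but it has a consequence that must be stated with it. The criterion is harder to meet, and at equal 60% agreement the planned size gives about 64% power with 114 evaluable per arm, or 71% with all 135. The statement that power exceeds 80% must therefore be restated. Keeping 80% power under this rule would need about 168 evaluable per arm (336 in total). If a one-sided 95% limit was meant, the type 1 error statement should say so. The need is then 132 per arm (264), and 114 per arm still falls short of 80%.
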